# **OBJECTIVES AND OUTCOME MEASURES**

| **Objectives** | **Outcome Measures** |
| --- | --- |
| ***Primary*** | |
| To assess if the CREED AF intervention improves exercise capacity (assessed by VO_2peak_) in AF patients listed for first-time AF ablation compared to standard care at 10 weeks (±2 weeks) post-ablation. | The VO_2peak_ is measured as described in Section 9.9 Cardiopulmonary Exercise Testing (CPET) at baseline and 10 weeks (±2 weeks) post-ablation which in the intervention arm coincides with two weeks after the last CREED AF intervention exercise session. |
| ***Secondary*** | |
| To explore if the CREED AF intervention improves short- and long-term EQ-5D-5L in AF patients listed for first-time AF ablation compared to standard care. | The EQ-5D-5L is a health status instrument made up of five dimensions: mobility, self-care, usual activities, pain/discomfort, and anxiety/depression, and a visual analogue scale (VAS). There are 5 response levels within each dimension.  The EQ-5D index value is computed according to the scoring algorithm from EuroQol. The value ranges from -0.148 (worst) to 0.949 (best).  Participants indicate their overall health on the day of questionnaire completion on a vertical EQ VAS which ranges from 0 (the worst health you can imagine) to 100 (‘the best health you can imagine’).  Short-term: change of EQ-5D index value and EQ VAS from baseline to 10 weeks post-ablation.  Long-term: change of EQ-5D index value and EQ VAS from baseline to 12 months post-ablation. |
| To explore if the CREED AF intervention improves short- and long-term 36-item short form health survey (SF-36) in AF patients listed for first-time AF ablation compared to standard care. | SF-36 is made up of eight domains (physical functioning, role-physical, bodily pain, general health, vitality, social functioning, role-emotional, and mental health). Each of the domain contributes to the Physical Component Summary (PCS) and Mental Component Summary (MCS) which ranges from 0 (worst) to 100 (best).  Short-term: change of PCS and MCS and each domain from baseline to 10 weeks post-ablation.  Long-term: change of PCS and MCS and each domain from baseline to 12 months post-ablation. |
| To explore if the CREED AF intervention improves short- and long-term Atrial Fibrillation Effect on Quality-of-Life (AFEQT) in AF patients listed for first-time AF ablation compared to standard care. | The AFEQT is an AF-specific health-related QOL made up of 3 subscales (symptoms, daily activities, and treatment concern). The transformed overall score ranges from 0 (complete disability) to 100 (no disability).  Short-term: change of AFEQT from baseline to 10 weeks post-ablation.  Long-term: change of AFEQT from baseline to 12 months post-ablation. |
| To explore the cost-effectiveness of the CREED AF intervention compared to standard care. | The incremental cost per quality adjusted life year (QALY) will be estimated. See details in Section 10.7. |
| To explore if the CREED AF intervention can decrease AF burden and recurrences following AF ablation, and reduce the requirement for redo-AF ablation. This will be assessed with a 1–7-day cardiac Holter monitor at 10 weeks (±2 weeks) and 12-months (±4 weeks) post ablation, and on review of patients’ medical records at 12-months. | Participants will be fitted with a Holter monitor at the 10-week and 12-month post-ablation follow-ups. Of the list of summary data over the time period it is worn by the participant, only the significant AF event and burden, and when it occurred will be recorded. |
| To explore if the CREED AF intervention has an impact on major adverse cardiovascular events (MACE) at the 12-month follow-up between both groups. MACE will be defined as individual outcomes and as a composite of hospital admission related to AF, non-fatal myocardial infarction, non-fatal stroke, cardiovascular death, and all-cause mortality. | Any occurrence of the following events:   - Hospital admission related to AF (from hospital records) - Non-fatal myocardial infarction (as above) - Any non-fatal stroke (as above) - Cardiovascular death (as above) - All-cause mortality (as above)   and when each occurred. |

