|  | To explore if CREED AF intervention has an impact on the short- and long-term recurrence of AF post-ablation and the need for redo-AF ablation. | AF recurrence and burden from data collected from a 1–7-day(s) cardiac Holter monitoring at 10 weeks (±2 weeks) and 12 months (±4 weeks) post ablation, and requirement for redo-AF ablation as documented in medical records reviewed at 12 months post-ablation. |
|  | To explore the impact of CREED AF intervention on relevant major adverse cardiovascular events (MACE) in AF patients. | MACE at 12 months post-ablation, defined as:   1. Hospital admission related to AF 2. Non-fatal myocardial infarction 3. Non-fatal stroke 4. Cardiovascular death 5. All-cause mortality |

Key Words: **AF ablation, Pulmonary vein isolation, VO2peak**

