The 1-to-1 education sessions in the CREED AF Intervention arm will be conducted by an exercise practitioner/researcher and will be performed either online, over the phone, or in-person. The sessions will incorporate comprehensive behavioural change and motivational strategies to improve patient adherence and compliance to risk factor modification with the aim of improving both short- and long-term adherence to exercise and lifestyle modification goals and reduce their exposure to lifestyle risk factors (e.g., smoking, alcohol consumption, weight reduction etc.). This will be guided by a participant workbook, and further sign-posting to support groups will be in accordance to individual participant’s requirements. A full compliance of education sessions is at least 2 sessions (of a total of 3; 66.7%) at each prehabilitation and rehabilitation intervention.

- 1. **Follow-up data**

In addition to cardiopulmonary exercise testing at 10 weeks follow-up post-ablation, all patients will also repeat the baseline questionnaires to assess their HRQoL, including the EQ-5D-5L, SF-36 and AFEQT, at significant intervals of the intervention journey (as outlined in the Schedule of Events). To assess for AF recurrence and burden, 7-day Holter ECG monitoring will be placed on patients at the 10 weeks and 12 months post-ablation follow-up appointments. The 10-week (±2 week) period will be seen as equivalent to a 3-month blanking period that is normally considered post-ablation in which presence of AF is not seen as a recurrence. The definition of an AF recurrence post-ablation will be an arrhythmia with the characteristics of AF that is either captured on a 12-lead ECG or documented to last for at least 30 seconds on ECG monitoring (1). At 12 months post-ablation, a retrospective review of medical records will be completed to collect data for study defined MACE. This will include, but will not be limited to, a review of clinic letters, medical coding, and A&E records.

- 1. **End of Study Definition**

The end of study definition will be when the last participant has completed their 12-month follow-up appointment and data collection post-ablation.

- 1. **Assessment and Management of Risk**

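### The protocol gives conflicting sources for AF recurrence; read as Holter-only, AF that returns and is successfully re-treated before the 12-month Holter is scored as no recurrence and zero burden

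*Protocol*

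**What the plan says.** Most of the protocol takes recurrence and burden from the Holter.

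- **Study Summary, secondary outcomes:** "AF recurrence and burden from data collected from a 1–7-day(s) cardiac Holter monitoring at 10 weeks (±2 weeks) and 12 months (±4 weeks) post ablation". The medical records are assigned to a different item, "requirement for redo-AF ablation as documented in medical records reviewed at 12 months post-ablation".
- **Objectives and Outcome Measures, outcome cell:** participants wear a Holter at the two visits, and of its summary data "only the significant AF event and burden, and when it occurred will be recorded".
- **Trial Procedures, Follow-up data:** "To assess for AF recurrence and burden, 7-day Holter ECG monitoring will be placed on patients at the 10 weeks and 12 months post-ablation". The records review has another stated purpose: "a retrospective review of medical records will be completed to collect data for study defined MACE".
- **Secondary outcome analysis:** recurrence and burden from the Holter are treated as a time-to-event estimand, and the proportion with a significant AF event is estimated by Kaplan-Meier.

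Other text is wider.

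- **Objectives and Outcome Measures, objective cell:** burden, recurrence and redo ablation are jointly assessed by Holter "and on review of patients’ medical records at 12-months".
- **Follow-up data, definition of recurrence:** AF qualifies if "either captured on a 12-lead ECG or documented to last for at least 30 seconds on ECG monitoring".
- **Schedule of Events:** the month-12 review of hospital records covers MACE and redo ablation, with an open-ended addition.

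Follow-up data also equates the 10-week (±2 weeks) period with the 3-month blanking period, during which AF does not count as a recurrence.

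**The concern.** The stated definition is wider than the source that most sections name. A 12-lead ECG showing AF at month 5 meets the definition, yet no sentence carries it into the recurrence outcome. Nor does any sentence say that a redo ablation or a cardioversion for AF counts as a recurrence, and cardioversion is not named as a data item.

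The objective is to learn whether the programme reduces short- and long-term recurrence, burden and redo ablation. Re-treatment changes the rhythm found at 12 months. If re-treated failures are scored as successes, the 12-month result reflects later care as well as the randomised programme. Under Blinding, the exercise physiologists leading the 10-week test are the only staff said to be blinded. Clinicians who decide on re-treatment may therefore know the allocation, and re-treatment rates could differ by arm.

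**Working it through.** The protocol states no figure for AF recurrence in this trial, so there is none to reproduce. The check is a reading of the text followed by an illustration.

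**1. One patient followed through the text.** Suppose the 10-week Holter is clean, AF returns at month 5 and is shown on a 12-lead ECG, redo ablation takes place at month 8, and the 12-month Holter shows sinus rhythm.

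- Definition in Follow-up data: recurrence at month 5.
- Study Summary, outcome cell and Secondary outcome analysis: no recurrence and zero burden; the redo is counted as a separate outcome.
- Objective cell: possibly a recurrence, since the records are named, but no rule says so.

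The same patient is scored differently depending on the section followed.

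**2. Effect of the blanking rule.** If AF in the 10-week window is not a recurrence, the 10-week Holter cannot score one. Only the 12-month Holter remains. The patient above is misclassified even if the 10-week Holter is allowed to count, because it was clean.

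**3. How many patients could be affected.** Eligibility Criteria gives a first-procedure success rate of about 40-80%, so 20-60% recur. Per arm this is 53 × 0.20 = 10.6 to 53 × 0.60 = 31.8, about 11 to 32 patients. Assume that 10-50% of recurrences are re-treated and in sinus rhythm at the 12-month Holter (not a document figure):

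- lowest: 106 × 0.20 × 0.10 = 2.1 patients;
- highest: 106 × 0.60 × 0.50 = 31.8 patients.

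So about 2 to 32 of 106 would be scored recurrence-free.

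**4. Effect on the comparison.** Observed recurrence = true recurrence × (1 − proportion re-treated × proportion restored to sinus rhythm). Assumed inputs: true recurrence 45% in control and 30% in intervention (a 15-point difference, risk ratio 0.67), with 70% of re-treated patients restored.

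| Re-treated, control / intervention | Observed control | Observed intervention | Difference |
| --- | --- | --- | --- |
| 35% / 35% | 0.45 × (1 − 0.35 × 0.70) = 34.0% | 0.30 × (1 − 0.35 × 0.70) = 22.7% | 11.3 points |
| 50% / 20% | 0.45 × (1 − 0.50 × 0.70) = 29.3% | 0.30 × (1 − 0.20 × 0.70) = 25.8% | 3.5 points |
| 20% / 50% | 0.45 × (1 − 0.20 × 0.70) = 38.7% | 0.30 × (1 − 0.50 × 0.70) = 19.5% | 19.2 points |

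With equal re-treatment the risk ratio stays at 0.67 and only the absolute difference shrinks. With unequal re-treatment the difference can shrink or grow. The formula also assumes that the 12-month Holter detects every recurrence that was not re-treated, which is optimistic for intermittent AF.

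**The case against.** The strongest reply is that the protocol does not fix a Holter-only source. The objective cell names medical records for burden, recurrence and redo together, the Schedule leaves the records review open-ended, and Follow-up data says its list of records is not exhaustive. This stands in part: a reader might infer that recurrence is read from the Holters alone, and the documents do not settle that. But the Study Summary splits the sources and gives the records only to redo ablation, so the sections conflict.

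A reader might also take the word 'only' in the outcome cell as excluding other sources. It does not; it limits which Holter summary data are kept. The Holter-only reading rests on the Study Summary, Follow-up data and Secondary outcome analysis.

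Nor are re-treated patients lost to the trial. Redo ablation is an outcome in its own right, and an AF-related admission is a dated MACE component. An outpatient cardioversion, however, need not appear under either, and the recurrence and burden results remain misclassified in all these cases.

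Detailed scoring rules can be left to the statistical analysis plan, which is not shown. That plan cannot repair conflicting sources in the protocol unaided, and it cannot analyse cardioversions or ECG findings that were never collected.

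Finally, a fixed-schedule Holter in both arms does not depend on clinician behaviour, which is a real merit in an open-label trial. It is a reason to keep the Holter-only analysis alongside the wider one.

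**Conclusion.** The point holds as an inconsistency between the definition of AF recurrence and the sources named for it. On the Holter-only reading, a patient whose AF returned and was successfully re-treated before the 12-month Holter is scored recurrence-free with zero burden.

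It is tempting to conclude that this biases the comparison towards no difference. The documents do not support that. They give no re-treatment or restoration rates, and the direction depends on how re-treatment differs between arms. The range of about 3.5 to 19 points around a true 15-point difference, and the 2 to 32 misclassified patients, rest on the stated assumptions and show only that the effect need not be small.

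The outcome is secondary and exploratory. The VO2peak primary analysis and its sample size are untouched. The change is worth making because it is cheap and partly concerns data collection, which is hard to repair afterwards.

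**What to change.** Reconcile the Study Summary, Schedule of Events, Objectives and Outcome Measures, Follow-up data and Secondary outcome analysis on one rule:

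- A recurrence is AF meeting the Follow-up data definition after the blanking period, found either on a study Holter or in the 12-month records review. From the records, count ECG-documented AF, AF admission, cardioversion for AF and redo AF ablation, each with its date.
- Add ECG-documented AF and cardioversion as data items in that review.
- Report the number re-treated by arm, and give 12-month burden with and without re-treated participants.
- Keep the Holter-only result as a sensitivity analysis, because re-treatment is partly clinician-driven in an open-label trial.

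This concerns how outcomes are scored, not how patients are treated. The cost is wording in the protocol and analysis plan plus two data items in a review that already covers clinic letters, coding and A&E records.

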# **STUDY DESIGN**

This is a single centre, prospective, randomised controlled trial.

# **STUDY SETTING**

The CREED AF study will run from University Hospitals Coventry & Warwickshire (UHCW) NHS Trust. There will be collaboration with Atrium Health, a non-profit exercise rehabilitation centre located in Coventry, UK. Atrium Health was founded by frontline NHS clinical staff to provide people with tailored exercise and education programmes.

# **ELIGIBILITY CRITERIA**

Eligible patients will be those suffering from AF (including long-standing AF) who are listed for a first-time AF ablation. Building upon existing evidence and input from our PPI, it was felt that due to the heterogeneity of AF presentations and our trial sample size being small it was preferable that the study population was homogenous i.e., only those with AF undergoing a first-time AF ablation. Although medical therapy remains the foundation of the treatment of AF, catheter ablation using Pulmonary Vein Isolation (PVI) is assuming an increasingly greater role (18). The success rate of a first-time AF ablation procedure for AF is estimated at ~40-80% at 1-2 years, after which there is attrition (recurrence of AF) over time; studies have associated this attrition to cardiac risk factors.

- 1. **Inclusion criteria**
- All patients AF listed for a first-time AF ablation procedure
- Patients aged ≥18 years
- Able to understand basic spoken and written English themselves, or with support from family and friends.
  1. **Exclusion criteria**
- Pregnancy
- Lack of capacity to consent and participate
- Presence of contraindications or limiting physical or mental health co-morbidity preventing travel, safe exercise, or productive engagement with the trial
- Unable to access online exercise and support sessions from home
- Participating in a research trial that will impact on their standard AF ablation procedure

# **TRIAL PROCEDURES**

- 1. **Screening**

University Hospitals Coventry and Warwickshire performs ~ 300 ablations per year. Delegated members of the research team, who are also members of the direct care team, will screen the list of participants who are referred to UHCW for an ablation procedure. If the participant meets the inclusion/exclusion criteria then the research team will provide the potential participant with the participant information sheet (PIS) and invitation letter, inviting them to take part in the study. Where applicable, an expression of interest form and consent form will also be provided. Potential participants can be approached either face-to-face during a standard care clinic appointment, or remotely using a method acceptable to the patient e.g., phone, post, email, video call. Reasonable effort will be made to contact the participant following provision of the PIS and invitation letter. Screening logs will be kept by the study team to provide information on patient eligibility, and reasons for non-participation, to inform future NHS service design. Patient’s sex and ethnicity will also be logged at screening to monitor inclusion.

- 1. **Recruitment**

Prospective participants who are eligible to participate will be contacted by a member of the research team to confirm if they are interested in taking part. The member of the research team will explain the study in more detail and answer any questions the prospective participant may have. During the initial consultation, the potential participant will have explained to them the full study procedures should they decide to join the trial. It will be made clear that they could be randomised to the control arm whereby they would not receive the exercise intervention, and only be required to complete the outcome assessments and one 30-minute risk management education session. The prospective participant will be given a suitable amount of time to consider joining the study and encouraged to ask questions. Following the initial consultation, the prospective participant will be invited to join the study. If they agree to take part, they can then be consented. If a participant is consenting over the phone, they will be asked to counter sign their consent form on their first study visit to the hospital.

- 1. **Payment**

Participants will be reimbursed their travel costs for travelling to and from the Atrium Health Centre, for the purpose of CREED AF exercise training visits. They will be reimbursed up to a maximum of £10 per visit to the Atrium Health Centre, which will cover the cost of travel (public transport or fuel) and parking. This can be claimed by the participant at the conclusion of each intervention period (e.g., end of prehabilitation and rehabilitation). We will aim to align hospital visits with standard of care, however if any additional visits to the hospital are required that are specifically for the purpose of the CREED AF study, then these travel visits will be reimbursed, after each visit. Participants will be required to keep a log of their travel expenses during their time in the study.

- 1. **Consent**

Prospective participants will be asked to confirm whether they have read and understood the PIS and will be encouraged to ask questions and be provided enough opportunities to discuss before deciding to take part in the study. Patients will be free to discuss the study with friends and family before reaching their decision.

After confirming the patient’s eligibility to take part, a qualified member of the research team, who has received training in obtaining informed consent, will obtain consent. Informed consent will be obtained prior to the participant undergoing procedures that are specifically for the purposes of the CREED AF study and out-with standard routine care at UHCW. The participant will be able to refuse to participate in the study without giving any reasons and this will not affect their standard treatment in any way.

If informed consent is initially obtained remotely e.g., consent statements agreed over the phone, the participant will be asked to counter sign their consent form on their first study visit to the hospital before starting any assessments. A copy of the signed consent form will then be provided to the participant.

The consent procedure will be undertaken by a delegated member of the research team and will involve:

- Discussion between the potential participant and an authorised individual who is knowledgeable about the research and about the nature and objectives of the trial and possible risks associated with their participation.
- Presentation of written material (e.g., information leaflet and consent document which must be approved by the REC and comply with GCP, local regulatory requirements and legal requirements).
- Opportunity for potential participants to ask questions.
- Assessment of capacity. For consent to be ethical and valid in law, participants must be capable of giving consent for themselves. A capable person will:
  - understand the purpose and nature of the research,
  - understand what the research involves, its benefits (or lack of benefits), risks and burdens,
  - understand the alternatives to taking part,
  - be able to retain the information long enough to make an effective decision,
  - be able to make a free choice,
  - be capable of making this specific decision at the time it needs to be made (though their capacity may fluctuate, and they may be capable of making some decisions but not others depending on their complexity),
  - where participants are capable of consenting for themselves but are particularly susceptible to coercion, it is important to explain how their interests will be protected.

Patients who are determined to lack capacity will be excluded from recruitment to the CREED AF study.

- 1. **Blood Tests**

Blood tests are performed as part of standard care for patients who are referred for first-time AF ablation. We will retrospectively collect data that is available on the patient’s hospital record from their pre-ablation blood test following consent. Biomarkers we are interested in including, but are not limited to full blood count, renal function, thyroid function, BNP, and Troponin.

- 1. **Randomisation**

Pre-randomisation eligibility checks will be carried out to ensure that potential participants meet the eligibility criteria and are not randomised in error. Written consent for entry into the trial and baseline assessments must be obtained prior to randomisation. Subjects will be randomised once they have been registered as eligible for randomisation and attended their baseline assessment.

After the baseline assessment, participants will be randomised on a 1:1 basis to the CREED AF intervention or usual care. Participants will be stratified by sex (male or female), AF type (Paroxysmal or Persistent), left ventricular ejection fraction (not impaired ≥50% or impaired <50%), and Amiodarone use (Yes or No).

Randomisation will be carried out using an online validated randomisation sequence generator, as part of the Electronic Data Capture system. The block sizes to be used in the randomisation sequence in the electronic data capture (EDC) system will be determined by the trial statistician prior to setting up the EDC.

Participants will be informed of their allocation to treatment in writing (e.g., email or post), with information on the next steps depending on their allocation.

- 1. **Blinding**

It is not possible to blind several members of the study team as they will directly be involved in the delivery of the prehabilitation and rehabilitation. Protecting our primary outcome measures, the exercise physiologists leading the cardiopulmonary exercise testing at the 10-week post-ablation follow-up will be blinded from the participant’s treatment allocation. We will endeavour to inform patients not to let the physiologists know their treatment allocation when communicating with them. We will record if a participant tells the follow-up exercise physiologist their allocation.

- 1. **Baseline data**

All participants will have the same baseline data collected following consent. This includes, but is not limited to: demographic data, medical history, current medications and details of their AF. All participants will be asked to complete a few validated questionnaires to assess their HRQoL, including the EQ-5D-5L, SF-36 and AFEQT. This initial dataset can be collected over the phone following consenting of the participant into the trial. The questionnaires can be posted to the participant to complete at home and return at a following clinic appointment or they can be emailed out to the participant to complete online using the EDC System.

- 1. **Cardiopulmonary Exercise Testing**

The CPET will be performed by both the control and intervention groups at baseline and 10 weeks (±2 weeks) post-ablation. The test will be used to assess exercise capacity and will give an indicator of the participant’s cardiorespiratory fitness. The tests will be performed at UHCW’s respiratory laboratory. The lab is UKAS accredited to IQIPS standard to perform CPET. The local UHCW standard operating procedure for CPET will be followed for all participants during their VO_2peak_ test. This information is available in full detail in a separate document, but briefly:

1. The participant will have their height and weight measured and information about the current medications collected.
2. They will have the procedure explained to them in full detail and any questions they have will be answered.
3. A spirometry measurement of forced vital capacity will be obtained before the CPET begins.
4. A 12-lead ECG will be attached to the participant.
5. A Hans Rudolph face mask will be fitted to the participant and baseline data collected.
6. A blood pressure cuff and pulse oximeter will be attached with measurements taken at baseline and during the test.
7. The exercise protocol will begin with increasing exercise intensity until the participant feels they cannot continue, when cadence falls by 5% or more or when the individual leading the exercise test requests it to be stopped.
8. Recovery period involving low intensity exercise.
   1. **Standard Care Group**

Participants who are randomised into the control group will complete the outcome assessments at baseline and 10 weeks (±2 weeks) post-ablation. Further HRQoL questionnaires and medical records will be reviewed at 12 months (±4 weeks) post-ablation. They will also receive a 30-minute 1-to-1 education session (remotely or in person) from a CREED AF practitioner before their AF ablation to go through the risk factors of AF and what they can do to improve their health. The session will involve a discussion with the participant around risk factors related to AF and recommendations for what actions the participant should take to minimise these factors, sign-posting to publicly available patient information leaflets (e.g. <https://heartrhythmalliance.org/aa/uk/resources/arrhythmia-alliance-patient-resources>). For the rest of the trial, they will follow the standard care pathway for ablation patients.

- 1. **Intervention Group**

The CREED AF intervention will involve 2 distinct intervention strategies that come together. These strategies are the exercise intervention and the education intervention. Participants who are randomised to this intervention will have an additional consultation with a member of the research team who will go over again in more detail what the CREED AF intervention is, and what it involves for the participant.

Exercise Sessions

*Format*: To ensure generalisability to the NHS, the underpinning framework of the CREED AF exercise intervention is based on UK cardiopulmonary rehabilitation guidelines and service delivery models (62).

*Programme Design*: Participants randomised to the CREED AF intervention can immediately join existing cardiopulmonary rehabilitation exercise programmes rather than waiting for the recruitment of sufficient numbers to form a discrete group of trial participants.

Individual assessment and exercise familiarisation

*Individual assessment*: A 1-to-1 online appointment with a CREED AF ‘practitioner’ (specialist cardiopulmonary clinical exercise physiologist or physiotherapist). Participants will undergo an ‘assessment,’ as per standard practice in UK cardiopulmonary rehabilitation programmes, to assess medical history, medication, and discussion of participant goals, expectations, fears, and concerns.

*Exercise prescription*: The CREED AF practitioner will prescribe a tailored, individualised exercise programme within pre-specified parameters, as outlined in the information sheet. Clinical information, data from the exercise assessment, and patient centred goal setting will be used to devise a safe and effective exercise prescription. There are no accepted guidelines for exercise training in patients due for ablation. Our intervention will be individualised and based on existing evidence in similar populations, our PPI sessions, and our centres’ expertise in the provision of exercise for clinical populations.

*Familiarisation*: Exercise will be delivered on a rolling basis, so a participant can immediately join a pre-existing cardiopulmonary exercise group that is at a similar physical level to them. During the first week of the programme, the clinical staff will assess their capability to carry out the prescribed exercise. Following this, the exercise that the participant is undertaking could be altered slightly to better suit their physical capabilities. The familiarisation period will enable participants to build confidence, whilst CREED AF practitioners refine and optimise the exercise prescription.

Exercise Programme (2-3 times/week for 6-8 weeks, pre- and post-ablation)

Exercise training will be facilitated by a trained CREED AF practitioner using:

1. Participant manual with details of the exercise programme, instruction on safe and effective exercise, and a logbook to self-record completed exercise. These materials will be provided to participants at the start of the intervention.
